### mHealth-based EDSS

Separate EDSS modules will be developed for NPHW and UPHC doctors. The software will be developed on an Android platform, optimised for 7-inch tablets. The EDSS will include a screening tool based on the Patient Health Questionnaire (PHQ-9) [41, 42] which has been validated in India [43]. The PHQ-9 is available in the two vernacular languages spoken in Vijayawada and New Delhi and has been validated as an excellent tool for screening depression among adolescents [44]. The diagnostic and management guidelines that will be used by the UPHC doctor are based on WHO’s Mental Health Gap Action Programme- Intervention Guide (mhGAP-IG) [45] and focus on three conditions: depression, other significant emotional or medically unexplained complaints and self-harm/suicide. The mhGAP-IG is in English. The algorithm will be modified based on multiple iterations and feedback from the research team and a psychiatrist and has been validated in a previous mixed methods study [46]. The treatment algorithm provides guidelines about both pharmacological and psychological treatment including referral to a mental health specialist. A traffic-light dashboard called the priority listing app will also be included to support NPHWs to follow up high risk individuals and act on the treatment provided by the doctors.

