The implementation of the mobile technology-based EDSS will include the following:Trained interviewers will administer the PHQ-9 to adolescents aged 10 to 19 years in the selected slum clusters to screen for depression and suicide/self-harm risk. They will use a tablet-based questionnaire to generate composite scores to identify ‘high-risk’ adolescents.NPHWs and doctors will be trained by the research team before the beginning of the intervention. Training of NPHWs and UHC doctors will be provided by in-person training and via the virtual conferencing platforms developed earlie r[24]. The NPHWs will then provide basic supportive advice such as engaging oneself in hobbies, strengthening social contact, and so on, and a referral to the UPHC doctor. High-risk adolescents will be electronically referred via the mHealth platform and provided with a paper referral card to take to the doctor.The UPHC doctor will then review adolescents at high risk as part of a health camp organised in the slum or examine the patient who may directly visit the UPHC. Data from adolescents at high risk will be uploaded, with their consent, to a secure health record using the Open Medical Record System (MRS) open source, electronic health record system.A decision support application based on WHO’s mhGAP-IG algorithm will be integrated in a tablet device and that will be used by UPHC doctors to diagnose and manage patients experiencing depression, other significant emotional or medically unexplained complaints and or having self-harm/suicide ideation. Doctors will use the depression, other significant emotional or medically unexplained complaints and self-harm/suicide modules of mhGAP-IG, especially related to adolescents. Adolescents at high risk of requiring medication can access these directly from the UPHC or purchase low-cost generic medication from a private pharmacy.For adolescents with complex needs, consultation with a specialist psychiatrist will be available as needed. The psychiatrist will also conduct case reviews via phone and/or video conferencing with the UPHC doctors to enhance their management skills. Alternatively, such adolescents can be referred by the UPHC doctor to a psychiatrist in the next tier of the public health system.NPHWs will conduct follow-up visits and assess treatment adherence using the traffic light system to guide them about the status of each high-risk adolescent catered to by a particular NPHW.

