### Both arms

For all UPHCs, that fall within the study sites, the implementing team will liaise with government and private pharmacies to ensure the availability of appropriate medications. We will also explore collaborative strategies with the Ministry of Health and Family Welfare of both states (Andhra Pradesh and Delhi), to enhance the availability of common psychotropic medications for adolescents as per the Essential Drugs List in the UPHCs. Detailed contact information will be collected from all participants, such that follow-up can be done. The study participants will be constantly followed up for their wellbeing by the NPHWs and will also provide a great deal of motivation and encouragement to them to seek help for their mental illness on a regular basis.

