### Adverse event reporting

Serious adverse events will be recorded after the start of the intervention phase. A serious adverse event is defined as death due to any cause in the intervention or control arm, hospitalisation due to psychiatric disorders, or a history of self-harm or attempted suicide during the intervention period. These events will be captured using a standardised case report form and reported to an independent Data Safety Monitoring Committee Chairperson on a monthly basis and Ethics Committee Chairperson within 24 h of the implementing team being aware of the incident. This data will be analysed during the Data Safety Monitoring Committee meetings that will be held on a quarterly basis.

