### Stopping rule

In order to address safety concerns, at least one interim analysis will be conducted with results reviewed by the Data Safety and Monitoring Committee (DSMC). If the interim analysis shows a benefit from the intervention the study will proceed as planned as the sustained effect at end of the study will remain an ongoing question. A recommendation to discontinue the study prematurely will be based upon there being clear evidence that the intervention provides harm. Although no formal/ binding stopping rules are suggested, an increase in the proportion of participants with a suicide risk score >2 at 3 and 6 months in the intervention arm of 3 standard deviations (a 2-sided *p* value < 0.0027) or more would be regarded as strong evidence of early harm. The DSMC will reveal the unblinded results to the Trial Steering Committee if, taking into account both statistical and clinical issues and exercising their best clinical and statistical judgement, the unblinded results provide sufficient evidence that the trial treatment is on balance harmful.

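### The serious adverse event definition leaves out non-fatal, non-psychiatric drug reactions other than self-harm, although drug treatment is a planned part of the intervention

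*Protocol article*

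**What the plan says.** The Adverse event reporting section gives the definition in full. It opens with "A serious adverse event is defined as death due to any cause in the intervention or control arm, hospitalisation due to psychiatric disorders" and closes with "or a history of self-harm or attempted suicide during the intervention period". Death counts whatever its cause, but hospitalisation counts only when the cause is psychiatric. There is no criterion for a life-threatening event.

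Reporting is tied to that list: "These events will be captured using a standardised case report form and reported to an independent Data Safety Monitoring Committee Chairperson", monthly, and to the Ethics Committee Chairperson within 24 hours of the team learning of the event. The committee's regular review uses the same material: "This data will be analysed during the Data Safety Monitoring Committee meetings that will be held on a quarterly basis".

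On drug treatment, the section mHealth-based EDSS says "The treatment algorithm provides guidelines about both pharmacological and psychological treatment including referral to a mental health specialist". It adds that adolescents who may require medication "can access these directly from the UPHC or purchase low-cost generic medication from a private pharmacy". Under Both arms, the team undertakes to work with pharmacies on supply and to explore ways "to enhance the availability of common psychotropic medications for adolescents as per the Essential Drugs List in the UPHCs".

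**The concern.** Medication is a foreseen route of care in this trial. It is prescribed by primary care doctors using a new tool, for participants as young as 10. The definition is built around psychiatric and suicidal outcomes, so a serious physical reaction to a prescribed drug, or an accidental overdose, may meet none of its criteria. A site applying the text exactly would not complete the form for such an event.

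Under Stopping rule, the DSMC has to decide whether the trial treatment does harm on balance. If one class of serious non-fatal harm is screened out before the data reach it, the committee makes that decision on an incomplete record. The Strengths and limitations section presents the results as evidence for a scalable programme. A report of no excess of serious events could be read as covering drug safety when part of it was never collected as safety data.

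**Working it through.** The article gives no figure to reproduce, and none can be derived: it states neither the proportion of participants expected to receive a drug nor any reaction rate. The check is to read the sections against each other.

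**Step 1. Is the list closed?** It is introduced as a definition, with no wording to show that the items are examples. The next sentence limits the form and the reports to those events. An article may leave detail to the full protocol, but here the definition itself is stated.

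**Step 2. Is drug exposure foreseen?** Yes. The decision-support algorithm covers pharmacological treatment, access to medication is described, and supply work is planned for all health centres in the study, control arm included. The gap therefore exists in both arms.

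**Step 3. Which serious drug-related events meet the definition?**

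| Event | Criterion met | Reported? |
|---|---|---|
| Death | Death from any cause | Yes |
| Psychiatric admission, even if drug-induced | Psychiatric hospitalisation | Yes |
| Suicide attempt or self-harm, including intentional overdose of a prescribed drug | Self-harm or attempted suicide | Yes |
| Non-fatal admission for a physical drug reaction | None | No |
| Non-fatal life-threatening reaction or accidental poisoning | None | No |

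**Step 4. Is there another route to the DSMC?**
- The named harm signal in the Stopping rule section is "an increase in the proportion of participants with a suicide risk score >2 at 3 and 6 months in the intervention arm". It does not measure physical drug reactions.
- The follow-up instruments under Data collection are the PHQ-9, KAB, BACE-TS and CD-RISC-10. None is described as recording adverse drug reactions.
- Visits and medications appear under Economic evaluation, as costs.
- High-risk adolescents have an electronic health record in the decision-support pathway, but the article does not link it to safety reporting.
- Ethical considerations commits the trial to ICMR guidelines and Good Clinical Practice in general terms. That adds no event category to the specific definition.

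The last two rows of the table have no described route to the committee.

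**Step 5. How many participants does the definition govern?** The high-risk cohort is 60 clusters × 33 = 1980. The Abstract plans an equal number not at high risk, so both cohorts together are 1980 + 1980 = 3960. This is the population under the definition, not an estimate of events missed.

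**The case against.** The strongest defence is that the sponsor chose a targeted list on purpose. The trial tests implementation strategies, and medicines are used under WHO mhGAP-based guidance; no investigational drug is under test. The high-risk cohort is selected partly on suicide risk, and the safety provisions concentrate on suicide and self-harm. The treatment sections do not contradict the safety section either. The issue is how far the definition reaches. All of this stands, and it makes the choice understandable. It does not give the DSMC a view of the two event types left out.

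A reader might go further and infer that drug exposure has no safety outcome short of death, or that a hospital stay caused by a prescribed drug is never recorded. The article does not support that. Psychiatric admission counts whatever brought it on, self-harm includes intentional overdose, and the suicide-item comparison is a further non-fatal signal. Some care contacts may also be held in the health record or the cost data, though not as safety reports. Nor does the article rank drug reactions above other harms of the intervention.

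A fair practical objection concerns load. Sending every admission among about 3960 adolescents to the Ethics Committee within 24 hours would be real work, and the low-risk cohort is not referred for medication through the decision-support pathway. This stands, and the fix takes account of it.

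**Conclusion.** The point holds in a narrow form. A non-fatal, non-psychiatric hospital stay or life-threatening event from a prescribed drug, other than self-harm, is outside the stated definition and is not reported to the DSMC as a serious adverse event in either arm. Deaths, psychiatric admissions and suicidal events linked to a drug are covered.

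The conclusion rests on two readings: that the list is exhaustive, as its wording indicates, and that no safety stream exists beyond those the article describes. If the full protocol has a wider definition, the article should be brought into line with it. The article provides no basis for a count of missed events.

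Sample size, power and the primary analyses are untouched. What is affected is the completeness of the DSMC's evidence and any later statement about serious harm. The change should be made before the intervention phase, because events not collected prospectively may be hard to recover.

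**What to change.** In the Adverse event reporting section, for both arms, add hospitalisation for any cause and any life-threatening event to the events recorded. Add two fields to the case report form: the cause of the event, and whether the participant was taking a psychotropic drug. Keep psychiatric admission and self-harm or attempted suicide as named subsets in the DSMC tables, so that the present focus is not lost.

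To contain the work, leave 24-hour Ethics Committee reporting as it is for the events already listed. For the added events, restrict it to those suspected to be related to a prescribed psychotropic drug. The rest can be tabulated by arm for the quarterly DSMC meetings.

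The cost is a reworded definition, two form fields and a modest rise in reporting work. Staff who look for psychiatric admissions must already ask about hospital stays. Some unrelated admissions will be recorded, and the cause field separates them. No treatment or clinical rule changes.

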### Stopping rule

In order to address safety concerns, at least one interim analysis will be conducted with results reviewed by the Data Safety and Monitoring Committee (DSMC). If the interim analysis shows a benefit from the intervention the study will proceed as planned as the sustained effect at end of the study will remain an ongoing question. A recommendation to discontinue the study prematurely will be based upon there being clear evidence that the intervention provides harm. Although no formal/ binding stopping rules are suggested, an increase in the proportion of participants with a suicide risk score >2 at 3 and 6 months in the intervention arm of 3 standard deviations (a 2-sided *p* value < 0.0027) or more would be regarded as strong evidence of early harm. The DSMC will reveal the unblinded results to the Trial Steering Committee if, taking into account both statistical and clinical issues and exercising their best clinical and statistical judgement, the unblinded results provide sufficient evidence that the trial treatment is on balance harmful.

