**Methods:**

The intervention will be implemented as a cluster randomised control trial in 30 slum clusters in each of the cities of Vijayawada and New Delhi in India. Adolescents aged 10 to 19 years will be screened for depression and suicide ideation using the Patient Health Questionnaire (PHQ-9). Two evaluation cohorts will be derived—a high-risk cohort with an elevated PHQ-9 score ≥ 10 and/or a positive response (score ≥ 2) to the suicide risk question on the PHQ-9, and a non-high-risk cohort comprising an equal number of adolescents not at elevated risk based on these scores.

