### Eligible population

#### High-risk cohort

All consenting adolescents aged 10 to 19 years will be eligible for screening for depression, or suicide/self-harm risk. The screening will help to identify both high-risk and non-high-risk cohorts. High risk is defined as presence of at least one of the two conditions:High risk of depression based on PHQ-9 score ≥10.Positive response (score ≥2) to the suicide risk question on the PHQ-9.

Field investigators will continue screening until they have identified about 990 adolescents per location at high risk of depression or self-harm/suicide. This will form the ‘high-risk’ cohort. Because there will be some delay (up to 12 weeks) between screening and randomisation the high-risk adolescents will be rescreened to assess if they still meet the inclusion criteria prior to randomisation as literature suggests that around 25% of individuals initially identified at high risk will no longer meet the high-risk criteria at three months [47]. Only those adolescents who continue to remain at high risk during re-screening will form part of the high-risk cohort.

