### Control arm

The control arm slum cluster will receive usual care (currently the usual care practice involves very little support for mental disorders and only those with severe disorders are referred to a mental health professional) from their UPHC and general psychoeducation through brochures and pamphlets only. As part of good clinical practice, adolescents identified at high risk for depression or self-harm/suicide will be advised to consult a doctor or mental health professional for further diagnosis and treatment. If any adolescent is identified with severe depression, (a score of >=15 on PHQ9) and/or at high risk of suicide (suicide score >=2) during the screening, they and their parents/guardians will be advised to seek professional help immediately. A list of health facilities (with contact details) where such treatment is available will be provided to them. Further, the implementing team will request NPHW to follow up with the adolescent and their families more intensively and recommend them to visit a doctor/psychiatrist immediately. The implementation team will check to see whether the NPHW has made follow-up visits to such adolescents.

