### Tools used for data collection

i)PHQ9—The PHQ9 consists of 9-items. The final score is calculated by assigning scores of 0, 1, 2, and 3, to the response categories of “not at all”, “several days”, “more than half the days”, and “nearly every day”, respectively. PHQ-9 total score for the nine items ranges from 0 to 27, and scores 5–9 indicate mild, 10–14 indicate moderate, 15-19 indicate moderately severe, and 20–27 indicate severe depression. This instrument will provide a reliable estimate of depression in the communities and also the proportion among the screen positive individuals who have accessed mental health services. A cut-off score of ≥5 is indicative of mild depression needing further follow-up and assessment by the NPHWs, whereas a score of ≥10 needs clinical assessment by a PHC doctor.ii)CD-RISC – 10 scale—This scale consists of 10 items measuring resilience. Responses are rated on a 5-point Likert scale, ranging from 0 (not true at all) to 4 (true nearly all the time). Each score has a minimum score of 0 and a maximum score of 4. The total scores are calculated by adding the scores of all 10 items. Higher scores suggest greater resilience and lower scores suggest less resilience, or more difficulty in bouncing back from adversity.iii)KAB scale—KAB is used to measure the knowledge, attitude and behaviour related to mental health, and is a 16-item questionnaire. 12 of the items ascertain mental health knowledge, attitude and behaviours to understanding stigma. It has two subgroups—the behaviour subgroup and the knowledge and attitude subgroup. The behaviour subgroup is based on the Reported and Intended Behaviour Scale which uses a 5-point Likert scale (ranging from ‘agree strongly’ which scored 1, to ‘disagree strongly’ which scored 5). Higher scores suggest increased stigma, except for those questions which had a negative connotation. The knowledge and attitude subgroups were identified based on discussion with experts hence does not have the properties of a scaleiv)BACE – TS scale—This is a 12-item questionnaire with a four-point Likert scale, with scores ranging from 0 to 4, which asks questions on the stigma associated with seeking help for mental illnesses. Higher scores suggest higher stigma.

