#### mHealth component (high-risk cohort)

##### Primary outcome

Proportion achieving remission (defined as PHQ-9 <5, and/or suicide risk score <2) at 12 months.

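### The harm benchmark counts only a suicide-item score of 3, although the protocol defines high suicide risk as a score of 2 or more everywhere else

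*Protocol article*

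**What the plan says.** The Stopping rule section of the protocol article provides for at least one interim analysis, reviewed by the Data Safety and Monitoring Committee (DSMC). It gives one numerical benchmark for early harm: "an increase in the proportion of participants with a suicide risk score >2 at 3 and 6 months in the intervention arm", with the increase set at 3 standard deviations or more (2-sided p < 0.0027). It introduces this with the caveat "Although no formal/ binding stopping rules are suggested" and leaves the decision to the committee's judgement.

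Tools used for data collection describes PHQ-9 scoring as "assigning scores of 0, 1, 2, and 3, to the response categories".

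The same suicide item appears with a cut-off in four other places:

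- Abstract, Methods (high-risk cohort): "a positive response (score ≥ 2) to the suicide risk question on the PHQ-9".
- Eligible population, High-risk cohort: "Positive response (score ≥2) to the suicide risk question on the PHQ-9".
- Control arm (who is told to seek professional help immediately): "at high risk of suicide (suicide score >=2) during the screening".
- mHealth component, Primary outcome: "Proportion achieving remission (defined as PHQ-9 <5, and/or suicide risk score <2) at 12 months".

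Adverse event reporting separately counts as serious adverse events deaths, psychiatric hospitalisation and "a history of self-harm or attempted suicide during the intervention period".

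**The concern.** On an item that stops at 3, a score above 2 and a score of 2 or more define different groups. The first is the top category alone; the second is the top two. The protocol treats the top two as high risk when it enrols adolescents, when it advises them to seek help and when it judges the suicide-item part of remission. It then uses the top category alone when it looks for harm.

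The trial recruits 10- to 19-year-olds partly because of suicide risk, and this is the only numerical harm criterion in the document. If the intervention moved adolescents from 0 or 1 up to 2, they would become high risk by the trial's own definition and the benchmark would not register it. An interim program or committee charter that copies the sentence would carry the same gap.

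**Working it through.** **1. The plan's own figure.** The section equates 3 standard deviations with a 2-sided p of 0.0027. Check: 2 × (1 − Φ(3)) = 0.0026998, which rounds to 0.0027. The threshold is internally consistent. Only the event definition is in question.

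**2. Which scores each rule includes.** Possible item scores are 0, 1, 2 and 3 (Tools used for data collection).

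| Use | Cut-off | High-risk scores implied |
|---|---|---|
| High-risk cohort (Abstract; Eligible population) | ≥2 | 2, 3 |
| Immediate-help advice (Control arm) | ≥2 | 2, 3 |
| Remission, suicide-item part (Primary outcome) | <2 is favourable | 2, 3 |
| Harm benchmark (Stopping rule) | >2 | 3 |

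The benchmark counts 1 of 2 high-risk categories. Score 2 is left out.

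**3. What the benchmark can register.** Let p2 and p3 be the proportions scoring 2 and 3 in each arm (I = intervention, C = control).

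- Under >2 the difference is p3(I) − p3(C).
- Under ≥2 the difference is [p2(I) − p2(C)] + [p3(I) − p3(C)].

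If p3(I) = p3(C), the first is 0 whatever p2 does, and the second equals p2(I) − p2(C).

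**4. Illustration with assumed rates.** The article gives no score distribution, so the rates here are assumptions: 5% score 3 in both arms, and 10% (control) versus 20% (intervention) score 2. The size follows Statistical considerations: 60 clusters allocated 1:1 give 30 per arm, and 27 high-risk participants per cluster give 30 × 27 = 810 per arm. The effective number is n_eff = 810 / (1 + 26 × ICC), and z = difference / √(2 × p̄ × (1 − p̄) / n_eff), where p̄ is the mean of the two arms' proportions.

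Under >2 the difference is 0.05 − 0.05 = 0, so z = 0 at any ICC.

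Under ≥2 the proportions are 0.15 and 0.25, so p̄ = 0.20 and 2 × p̄ × (1 − p̄) = 0.32:

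| ICC | n_eff per arm | z under >2 | z under ≥2 |
|---|---|---|---|
| 0 | 810 | 0 | 0.10 / √(0.32/810) = 5.03 |
| 0.02 | 810 / 1.52 = 532.9 | 0 | 0.10 / √(0.32/532.9) = 4.08 |
| 0.1 (the protocol's planning value) | 810 / 3.6 = 225 | 0 | 0.10 / √(0.32/225) = 2.65 |

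Under these assumptions, a doubling of participants at score 2 is invisible to the benchmark as written. With ≥2 it passes 3 standard deviations at the two lower ICCs and reaches 2.65 at 0.1.

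**The case against.** The strongest reply is that cut-offs may differ by purpose. For the PHQ-9 total the protocol uses ≥10 for eligibility, ≥15 for immediate-help advice and <5 for remission. A safety committee might want only the most severe suicide-item category, particularly in a cohort partly selected for scoring 2 or more. The section does ask for strong evidence, and a condensed article may leave the reason to the full protocol or a charter.

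This reading is possible, but nothing in the text supports it. The total-score cut-offs are tied to stated severity levels, whereas the suicide item has one boundary everywhere else. The demand for strong evidence is already met by the 3 standard deviation threshold. The point is also not a missing rationale: the stated cut-off disagrees with the document's own definition of high risk.

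Three parts of the objection stand:

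- **Consequence.** The guide is non-binding, the committee judges unblinded results, and it receives serious adverse events separately. Those events record acts, admissions and deaths, however, and do not replace a measure of rising ideation.
- **Size.** The zero result needs equal proportions at score 3. A real worsening could raise both categories, and the benchmark would then pick up part of it.
- **Power.** In the illustration, the corrected cut-off still falls short of 3 standard deviations at an ICC of 0.1. Correcting it does not guarantee a signal, but it lets these adolescents count.

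**Conclusion.** The point holds and should be fixed. As written, the only numerical harm benchmark counts score 3 and omits score 2, which the protocol itself calls high risk. The mismatch follows from the item scoring and the stated cut-offs alone. It does not depend on sample size, ICC or the assumed rates.

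The practical size is unknown because no score distribution is given. At the extreme, with equal proportions scoring 3, the benchmark reads 0 standard deviations for any between-arm difference at score 2. Eligibility, the primary analysis, the sample size and the 3 standard deviation threshold are unaffected. A slip in the symbol is the likeliest explanation, though the text does not prove it.

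**What to change.** In the Stopping rule section, replace the cut-off >2 with ≥2, and make the same change in any DSMC charter or interim analysis program that repeats it. Keep the benchmark of 3 standard deviations (2-sided p < 0.0027). The same sentence can also make clear that the increase is intervention versus control at 3 and 6 months.

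If the sponsor did intend score 3 alone, the section should say so and give the reason.

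The cost is one symbol in each document that carries the rule. No extra data are needed, because Data collection already schedules the PHQ-9 at 3 and 6 months.
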